## Methods

### Design, Setting, and Recruitment

Because we are interested in comparing the effectiveness, rather than the efficacy, of the two training methods, we are using a pragmatic randomized controlled trial (RCT) design. The study setting is a large mental health hospital in Ontario, Canada, which delivers inpatient, outpatient, and emergency health care across a wide range of patient populations.

Newly hired staff that are classified as clinical direct service staff must undergo 2 weeks of onboarding, which includes the trauma-informed de-escalation education for safety and self-protection (TIDES) program. Within those 2 weeks, physical skills training is a full-day, in-person session scheduled on the last day. Because the onboarding is tightly scheduled, there is limited time for the typical processes of providing information about the study, gaining agreement and informed consent, and randomization. Consequently, the following procedures have been introduced.

Prior to the 2-week onboarding training, all newly hired clinical direct-service staff will be randomly assigned to their physical skills training session, and the physical skills training sessions will be randomly assigned to either BST or TAU. On the day before the physical skills session, the study will be introduced by a research team member to all attendees at the end of the last session on the previous day; during that introduction, consent will be obtained via a WebEx poll to send interested attendees a copy of the informed consent, and all attendees will be informed that a question-and-answer session along with obtaining informed consent will be carried out before the start of the physical skills session the next day, and then the informed consent form will be emailed to those who provided permission.

Just before the physical skills session, questions about the study or informed consent will be answered, and one-on-one meetings will be conducted with each attendee in a separate room to further review the informed consent and to sign indicating whether they agree or decline to participate in the study. This procedure is designed to protect against attendees identifying who is involved in the study (hereafter “study participant”) and who is not (hereafter “trainee”).

### Ethical and Safety Considerations

This study was internally funded and has been approved by the CAMH Research Ethics Board (#101-2020).

The study processes are designed to ensure that all attendees receive the same attention from the research team and facilitators and the same assessments during the training sessions. The goals are to provide equivalent training experiences, regardless of whether the person is a study participant or a trainee and regardless of whether they are in a TAU or BST session, as well as to minimize the possibility that attendees can identify who among them are or are not study participants. For example, in gaining informed consent, all attendees meet one-on-one privately with a research team member, and all sign the consent form by indicating whether they agree or decline to be study participants. In addition, skill assessments for all attendees are done individually in a separate room, but only the study participants (ie, those providing consent) are videotaped.

### Sample and Sample Size

Potential study participants include all newly hired clinical staff attending the mandatory training. There are no exclusion criteria (except the attendee’s desire not to be a study participant).

There is no published information on the expected effect size of BST versus other training methods. Indeed, most of the published BST studies have focused on efficacy and consequently have involved relatively small sample sizes. Consequently, we have opted for a sample size of 80 participants total (ie, 40 each in the BST and TAU groups) consistent with sample sizes providing 80% power for an expected medium to large effect size [25].

Recruitment began in January 2021, after REB approval was received. We reached our recruitment goal in September 2021.

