**Methods:**

We are using a pragmatic randomized controlled trial design. New staff registering for their mandatory safety training are randomly assigned to sessions which are, in turn, randomly assigned to either the BST or TAU conditions. Attendees are informed and consented into the study at the beginning of training. Differences between those consenting and those not consenting in terms of role and department are tracked to flag potential biases.

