There is a large body of evidence that indicates that individuals who receive BST demonstrate significant improvement in targeted skills posttraining and maintain those skills over time and across settings [21-23]. This model has been used to train a wide range of participants including behavior analysts, parents, and educators to build safety-related skills and manage aggressive behavior [21,24].

The objective of this study is to compare the real-world effectiveness of BST and TAU in terms of physical safety skills acquisition and retention after 1 month as well as staff confidence in their use of these skills.

The following are the null hypotheses being tested: there will be no significant differences between BST and TAU in terms of (1) the competence scores or the percentage of study participants who attain mastery (predefined as a score of 80% or higher) for self-protection or team control physical skills at the end of the mandated training session; (2) the competence scores or the percentage of study participants that continue to demonstrate mastery at 1 month posttraining for either self-protection or team-control skills (retention); and (3) the percentage of study participants who express confidence in their skills at 1 month posttraining.

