The checklists (see self-protection checklist example, Multimedia Appendix 1) will be used during training for the BST sessions and for the baseline, posttraining, and 1-month study assessments for all study participants. On the training day, attendees will be asked individually to go to a separate room. They will be asked once to demonstrate each of the 11 skills prior to the start of training for baseline and just after the training for posttraining. Only those attendees who have consented to be study participants will have their baseline and posttraining assessments videotaped. For the 1-month follow-up, study participants will be asked to come in to have their skills assessed and videotaped. Videotaping will be done through WebEx (Cisco) and will be rated by a research team member using the predefined competency checklists. On these checklists, each skill component will be judged to be performed “correctly” or “incorrectly.” The final competency rating for each skill will be the percent of its component skills that were rated as correctly performed.

The reliability and validity of these ratings will be assessed using IOA calculations [28]. Prior to the study, raters had been trained on a test set of videotapes drawn from a previous study and had reached agreement levels of at least 90% for self-protection and team-control skills. For this study, all videotapes are rated by a primary rater. At the same time, a 30% random sample of videotapes from training months 1, 3, 4, 6, and 9 will be independently rated by a designated secondary (reliability) rater. IOA with the ratings from the primary rater will be calculated after every 2 videotapes rated by the secondary rater and, if the IOA is less than 90%, a recalibration discussion is held and recorded between the 2 raters with a third neutral rater available if needed to resolve any remaining differences. Recalibration decisions are then applied to all subsequent videotape ratings.

A predetermined threshold of 80%, consistent with clinical practice [29,30], is then applied to each competency rating to define skill mastery. Retention between posttraining and the 1-month follow up is measured in terms of whether the competency ratings changed as well as whether the percentage of study participants meeting the mastery threshold has changed.

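### The stated 80% power for 80 participants holds at d of about 0.63 only for independent, complete data, and allows for neither session-level allocation nor loss at 1 month

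*Protocol article*

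**What the plan says.** Sample and Sample Size reports that "There is no published information on the expected effect size of BST versus other training methods". It then says "we have opted for a sample size of 80 participants total (ie, 40 each in the BST and TAU groups"), a number described as "consistent with sample sizes providing 80% power for an expected medium to large effect size". It gives no numerical effect, significance level, ICC, design effect or allowance for loss.

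Two other parts of the article bear on this:

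- **Allocation.** The Abstract (Methods) says new staff "are randomly assigned to sessions which are, in turn, randomly assigned to either the BST or TAU conditions". Design, Setting, and Recruitment repeats that "the physical skills training sessions will be randomly assigned to either BST or TAU". Under Interventions, each session has two facilitators, each training half of the attendees, and in-person numbers are capped at 10 including the trainer.
- **Follow-up.** Under Variables Assessed, "For the 1-month follow-up, study participants will be asked to come in to have their skills assessed and videotaped". The Introduction places hypothesis 2 (retained competence and mastery) and hypothesis 3 (confidence) at 1 month posttraining. Hypothesis 1 concerns the end of the training session.

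Recruitment reached its goal in September 2021, and data collection was complete by May 2022.

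**The concern.** A size of 40 per arm is what a plain two-sample comparison needs when people are randomised one by one and everyone is measured. Here the arm is assigned to a session, and people in a session share facilitators, so their outcomes may be correlated. The comparison between arms then carries session-to-session variation and has few degrees of freedom. This affects all three hypotheses. Loss before the return visit further reduces the data for hypotheses 2 and 3.

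What is at stake is interpretation. With no published effect size to lean on, this sentence is the reader's only guide to what a null result means. If the stated power is too favourable, a non-significant difference may be read as stronger evidence against a useful training benefit than it is.

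**Working it through.** **Inputs from the article:** 40 per arm; 80% power; sessions allocated to arms; an effect described only as "an expected medium to large effect size".

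**Assumptions, not in the article:** two-sided alpha of 0.05 (the null hypotheses are worded as "there will be no significant differences between BST and TAU"); conventional medium d = 0.5 and large d = 0.8; ICC 0.02 to 0.10; 16 sessions of 5 or 10 sessions of 8 participants (both give 80); 20% loss at 1 month; baseline correlation r = 0.5 or 0.6.

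**Step 1. Reproduce the stated figure.** For a two-sample t test with n per arm, the noncentrality is d × √(n/2). With n = 40 this is d × √20 on 78 degrees of freedom.

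- 80% power is reached at d = 0.634 (0.626 by the normal approximation).
- Power is 60% at d = 0.5 and 94% at d = 0.8.

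So 40 per arm gives 80% power at an effect between medium and large, with nothing to spare at that effect.

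**Step 2. Add session allocation.** The design effect is DE = 1 + (m − 1) × ICC, with m participants per session. The noncentrality becomes d × √(20/DE), on (sessions − 2) degrees of freedom.

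| Layout | ICC | DE | Detectable d (80% power) | Power at d = 0.634 |
|---|---|---|---|---|
| 16 × 5 | 0.02 | 1.08 | 0.70 | 72% |
| 16 × 5 | 0.05 | 1.20 | 0.74 | 67% |
| 16 × 5 | 0.10 | 1.40 | 0.80 | 61% |
| 10 × 8 | 0.02 | 1.14 | 0.76 | 64% |
| 10 × 8 | 0.05 | 1.35 | 0.83 | 57% |
| 10 × 8 | 0.10 | 1.70 | 0.93 | 48% |

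Part of the loss comes from the degrees of freedom alone: for 10 sessions with ICC = 0, the detectable d is already 0.716.

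**Step 3. Add loss at 1 month.** A 20% loss leaves 40 × 0.8 = 32 per arm. Without clustering the noncentrality is d × √16 and the detectable d is 0.71. With ICC 0.05 and session sizes reduced in proportion:

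- 16 sessions of 4: DE = 1 + 3 × 0.05 = 1.15, detectable d about 0.81.
- 10 sessions of 6.4: DE = 1 + 5.4 × 0.05 = 1.27, detectable d about 0.90.

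**Step 4. Allow for baseline adjustment.** Adjusting for a baseline measure with correlation r multiplies the variance by (1 − r²), so the detectable d is multiplied by √(1 − r²). With r = 0.5 the factor is √0.75 = 0.866.

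- Independent data: 0.634 × 0.866 = 0.55.
- 16 × 5, ICC 0.05: 0.738 × 0.866 = 0.64.
- 10 × 8, ICC 0.05: 0.832 × 0.866 = 0.72.

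**Step 5. Power at a medium effect (d = 0.5).** Unadjusted, it is 60% with independent data, and 48% (16 × 5) or 40% (10 × 8) at ICC 0.05. With baseline adjustment at r = 0.6 it is about 79% with independent data, and 66% or 56% at ICC 0.05.

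These figures apply to a standardised mean difference, such as a competence score. The percentages attaining mastery or expressing confidence would need their own calculation.

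**The case against.** The strongest reply is that nothing has been miscalculated. A reader might infer that the figure is an arithmetic error because power at d = 0.5 is only 60%, and 64 per arm would be needed there. The article does not support that inference. It does not claim 80% power at d = 0.5, and an effect between medium and large fairly covers 0.63. This part of the reply stands.

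A reader might also infer that the trial could detect only a large effect. That is not established either. Several scenarios above leave the detectable d at or below 0.8, and at d = 0.8 the 16 × 5 layout keeps 86% power at ICC 0.05 and 80% at ICC 0.10. Session count, ICC and return rate are all assumed. Staff are randomised to sessions, so there are no pre-existing groups, and correlation can arise only from shared delivery. The planned repeated measures analysis uses baseline data, and at r = 0.5 it would bring 16 × 5 at ICC 0.05 back to d = 0.64. All of this is fair and limits the size of the problem. The rescue is partial, however: r is also unstated, and the same adjustment leaves 10 × 8 at 0.72.

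Finally, the full protocol may hold the missing inputs, and 80 might have been chosen with a larger effect and some allowance in mind. The article does not say so. The point is not that an ICC is missing from a condensed article, but that the power it states is given without regard to the allocation and follow-up it describes.

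**Conclusion.** The point holds as a matter of design assumptions. The stated 80% applies at d of about 0.63 only if outcomes are independent and complete. At that effect, unadjusted power is below 80% under any positive ICC or any loss; the direction does not depend on the assumed values. The size does. With ICC 0.02 to 0.10, the detectable d moves from 0.63 to 0.70–0.80 (16 sessions of 5) or 0.76–0.93 (10 sessions of 8). It is 0.71 with 20% loss alone and about 0.81–0.90 with 20% loss and ICC 0.05. Clustering bears on hypothesis 1 as much as on hypotheses 2 and 3; only the loss is specific to 1 month. Baseline adjustment could recover some or, in favourable cases, nearly all of the clustering loss.

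**What to change.** Keep the 80 participants and change the text:

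1. State the assumed effect and significance level, and say that 40 per arm gives 80% power at d of about 0.63 only for independent, complete data.
2. Report the detectable effect using the actual number of sessions, a range of ICCs such as 0.02 to 0.10, and the actual 1-month return rate. Session numbers and return rate should be available, since data collection is complete.
3. Show baseline-adjusted figures alongside, with the assumed or observed correlation stated.
4. Say that a non-significant result does not exclude a medium effect.

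This needs no further enrolment or data collection. The cost is a less favourable stated power.

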### Interventions

Both the TAU and BST methods teach the same skills for protecting a person against aggression (eg, someone attempting to punch or choke the staff member) as well as to help a team of staff members physically restrain a patient who is becoming an increased risk of harm to self or others. There are 11 target skills (6 for self-protection and 5 for team-control) that are mandatory for all newly hired staff (Textbox 1). Each skill has a number of defined components, and the same sequence of steps is followed to teach each component. However, the 2 training methods differ in how these steps are administered and monitored (Table 1). The BST protocol involves attendees actively performing the targeted skills through a loop involving instruction, modeling, practice, and feedback using competency checklists [20]. This is continued until the competency of the target skill is demonstrated based on the observation of the trainer [20]. While the common practice as described in the literature is for the attendee to demonstrate successful performance of a skill 2 to 3 times before moving to the next skill on the checklist [26], we have chosen a more stringent threshold of requiring correct execution 5 times consecutively with the expectation that this will further consolidate skill acquisition and possibly retention. In contrast, TAU does not assess competency or require trainees to reach a specific level of competence for a skill before moving on to the next skill. It does, however, include modeling, practice, and feedback.

Each training session is run by 2 facilitators, each training half of the attendees to make the most efficient use of the allotted time. To be compliant with COVID-19 restrictions at the time of the study on the numbers of in-person attendees (maximum of 10 individuals including the trainer), 1 trainer is present at the session, while the other delivers the same material virtually.

List of 11 target skills.
**Self-protection skills**
Same-side push/punch/grab defenseCross-arm grab defenseRoundhouse or open-handed slap defenseSame-side grab defenseTwo-handed front choke defenseRear choke defense
**2-5–person team control (physical restraint) skills**
Level 1, 2-person team controlLevel 2, 2-person team controlLevel 3, 2-person team controlAdditional hand controlsAnchor

**Table 1 table1:** Comparison of training-as-usual (TAU) and behavioral skills training (BST) training steps.

Training strategy	TAU	BST
Target physical skills (self-protection and 2-5 person team-control)	Yes	Yes
Description of skill	Verbal with no structure	Verbal and written with systematic step-by-step instruction
Demonstration of skill by trainer	Yes	Yes
Practice of skill	Two stages (controlled practice and free practice)	Practice opportunities
Feedback	General feedback	Specific feedback using competency checklist
Repetition of description, demonstration, practice, and feedback	At the instructor’s discretion	Yes, the learner must demonstrate correct performance of 80%-100% of component steps 5 times consecutively before moving to train for the next skill
Use of competency checklist	No	Yes
Predetermined mastery criteria for each skill	No, attendees practice until the end of the allotted time	Yes, mastery for each skill defined as demonstrating correct execution of 80%-100% of component steps 5 times consecutively

### Variables Assessed

The variables to be assessed include skill competence, mastery, and retention; participant confidence in using each skill; the frequency of skill use in the previous month; and overall satisfaction with the training. Skill competence, mastery, and retention will be evaluated using checklists which were created guided by the considerations proposed by Stufflebeam [27] as well as through consultations with 2 coauthors who are board-certified behavior analysts (KB and LB). These are designed to evaluate the 11 mandatory skills being taught in the TIDES training program. The checklist creation process involved the following steps: (1) observing the training experts performing the skills and consulting with them; (2) having the organizational experts and trainers define and agree to the written descriptions in the training curriculum of the mandatory 11 target skills; (3) presenting the checklist drafts to key organizational stakeholders (professional practice office, union representatives, staff coaches, and executive leadership); (4) field-testing the resulting checklists in the mandatory staff training and making appropriate revisions; (5) and finally, making final edits based on the results of the interobserver agreement (IOA) assessment (please see further description of IOA below).

The questions assessing participant confidence, the frequency of skill use in the previous month, and overall satisfaction with the training are either adapted from existing questions used in the research team’s department or developed specifically for this study. Where applicable, 10-point Likert scales were used to improve accuracy.

The checklists (see self-protection checklist example, Multimedia Appendix 1) will be used during training for the BST sessions and for the baseline, posttraining, and 1-month study assessments for all study participants. On the training day, attendees will be asked individually to go to a separate room. They will be asked once to demonstrate each of the 11 skills prior to the start of training for baseline and just after the training for posttraining. Only those attendees who have consented to be study participants will have their baseline and posttraining assessments videotaped. For the 1-month follow-up, study participants will be asked to come in to have their skills assessed and videotaped. Videotaping will be done through WebEx (Cisco) and will be rated by a research team member using the predefined competency checklists. On these checklists, each skill component will be judged to be performed “correctly” or “incorrectly.” The final competency rating for each skill will be the percent of its component skills that were rated as correctly performed.

The reliability and validity of these ratings will be assessed using IOA calculations [28]. Prior to the study, raters had been trained on a test set of videotapes drawn from a previous study and had reached agreement levels of at least 90% for self-protection and team-control skills. For this study, all videotapes are rated by a primary rater. At the same time, a 30% random sample of videotapes from training months 1, 3, 4, 6, and 9 will be independently rated by a designated secondary (reliability) rater. IOA with the ratings from the primary rater will be calculated after every 2 videotapes rated by the secondary rater and, if the IOA is less than 90%, a recalibration discussion is held and recorded between the 2 raters with a third neutral rater available if needed to resolve any remaining differences. Recalibration decisions are then applied to all subsequent videotape ratings.

A predetermined threshold of 80%, consistent with clinical practice [29,30], is then applied to each competency rating to define skill mastery. Retention between posttraining and the 1-month follow up is measured in terms of whether the competency ratings changed as well as whether the percentage of study participants meeting the mastery threshold has changed.

Study participants complete self-reported evaluation forms covering descriptive information, confidence, training satisfaction, and frequency of skill use. The participants also provide information regarding their professional role and service department at CAMH. For confidentiality reasons, personal characteristics such as age and gender or sex were not provided to the research team, and, for the same reasons, we chose not to collect this information. All participants are asked to evaluate their confidence on a 0-10–point scale (0=not at all confident to 10=extremely confident) in using the 11 self-protection and team-control skills at baseline, immediately after the training, and at 1-month follow-up (Multimedia Appendix 2). All participants were asked to rate for satisfaction with the training on a 4-point scale immediately after the training and 1 month later. The number of times in the past month that self-protection or team-control skills were used is asked at baseline and 1-month posttraining. Finally, an open-ended item is provided in the posttraining assessment form for any comments that trainees want to communicate to the facilitators.

